#### Randomization of participants

Participants will be randomized to a treatment arm at the baseline visit, which will be conducted at their own GP practice (see Measurement of outcomes [Visit 1, Baseline] for details). The RA will give eligible patients who are willing to participate in the trial an opaque A4 sealed envelope, which will contain a color-coded randomization card. The envelopes will be numbered in sequence. We will use block randomization of randomly sequenced blocks of 2 and 4 stratified by GPs, which will balance individual consulting styles. The trial statistician will be responsible for the production of randomization schedule, prior to recruitment.

The RA will ask patients to give the sealed envelope to their GP upon entering their consultation. The card inside the sealed envelope will reveal to the GP, but not the patient, which intervention to deliver. We will ask GPs not to open the randomization envelope until they are satisfied that it is suitable for the patient to be included in the trial (that is, after they have addressed the patient’s primary reason for visiting them and feel that it would be clinically appropriate to offer a brief intervention at this time to this patient - see Exclusion criteria above; once the randomization envelope is opened then the patient has been enrolled in the trial. It would undermine the ability of the study to detect differences between the arms if we enrolled participants who did not receive an intervention. Attached to the outside of each randomization card envelope will be a detachable ‘patient withdrawal card’. The RA will discretely write the patient’s weight and BMI on the back of the withdrawal card before handing the sealed envelope to them so that the GP will be aware of their up-to-date measurements, if required, during the consultation. Furthermore, there will be a tick box option on the card for GPs to select if they did not randomize the patient in to the trial, indicating that the person has not been randomized and therefore not enrolled. The tick box will indicate the reason for non-enrolment (that is, clinically inappropriate, not appropriate in the consultation or special reasons). If ‘special reasons’ is selected, the GPs will be asked to state why, if they can without breaking patient confidentiality, in the space provided. The sealed envelope and withdrawal card would be returned to the RA by the patient after their consultation (see Measurement of outcomes [Visit 1, Baseline]) and the envelope will then be replaced at the top of the randomization envelope pile for use by the next appropriate potential participant.

To examine the fidelity of the intervention, the brief-intervention component of a proportion of consultations by each GP will be audio-recorded (see Treatment providers below). If an audio recording is required, a card will be attached to the randomization card inside the randomization envelope reminding the GP to turn on the audio-recorder at the appropriate time during the consultation. If a patient has not consented to audio-recording of the brief intervention, the GP will be alerted to this by a sticker on the randomization envelope.

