#### Exclusion criteria

The participant may not enter the study if any of the following apply:

• Pregnant or intending to become pregnant during the trial period (that is, the next 12 months).

• Currently or within the past 3 months participated in a weight management program (including pharmacotherapy or bariatric surgery).

• Unable to understand and speak English sufficiently to give informed consent and complete the research assessments.

• Visiting the GP for weight management.

• The GP deems it inappropriate to make an opportunistic intervention on weight management. This includes personal medical reasons known to the GP, such as an eating disorder, or reasons related to the consultation (for example, the patient has become distressed and it would seem insensitive to make such an intervention at that time). If the GP does not consider it appropriate, then the patient will not be enrolled and randomized into the trial (see Randomization of participants below).

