#### Unblinding

Due to the nature of this trial, it is necessary for the GPs and RAs to be aware of the patient’s treatment group allocation to ensure the correct intervention is provided. Thus, these personnel cannot be blinded to treatment. Patients and the members of the research team that will conduct follow-up assessments, however, will be blinded to treatment allocation.

As this is an open label trial the issue of unblinding the clinicians caring for the patient does not arise.

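### Blocks of 2 and 4 within each GP let the GP who decides on enrolment often guess the next allocation

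*Protocol article*

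**What the plan says.** The arrangement is spread over three sections of the protocol article.

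- **Randomization of participants, sequence:** "We will use block randomization of randomly sequenced blocks of 2 and 4 stratified by GPs". The stated reason is to balance consulting styles. Each patient carries "an opaque A4 sealed envelope, which will contain a color-coded randomization card", and the envelopes are numbered in sequence.
- **Randomization of participants, knowledge of the arm:** "The card inside the sealed envelope will reveal to the GP, but not the patient, which intervention to deliver". The section on unblinding says of GPs and RAs that "these personnel cannot be blinded to treatment".
- **Randomization of participants, enrolment decision:** "We will ask GPs not to open the randomization envelope until they are satisfied that it is suitable for the patient to be included". Opening the envelope is the moment of enrolment. If the GP declines the patient, a tick box on the detachable outside card gives the reason. The unopened envelope goes back to the RA, and "the envelope will then be replaced at the top of the randomization envelope pile".
- **Exclusion criteria:** the decision is a matter of judgement. A patient is out if "The GP deems it inappropriate to make an opportunistic intervention on weight management", for medical reasons or for reasons to do with that consultation.

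**The concern.** Sealed envelopes hide the next card but not the pattern of the cards already opened. Here one person holds all the roles that concealment is meant to keep apart. The GP is the stratum, has seen every earlier allocation in it, and decides whether the next patient enters. In very small blocks the earlier cards say a good deal about the next one.

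If the suitability decision leans on the expected arm, even without intent, the two arms may differ in motivation or in likely uptake of a referral. The primary ANCOVA adjusts for baseline weight, which does not capture either. The sample size section shows why this matters: the planned effect runs through uptake, with 30% assumed to take up referral in the support arm and 10% assumed to try to lose weight in the control arm. A larger sample would not reduce such a bias.

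**Working it through.** The protocol gives no figure for predictability, so there is none to reproduce. The input that matters is the number of participants per GP.

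**1. Participants per GP** (section on participant recruitment rate). Nine adults per session, 25% obese, 75% agreeing: 9 × 0.25 × 0.75 = 1.69 per session. Six sessions give 6 × 1.69 ≈ 10.1. As a check, 1,824 / 1.6875 = 1,081 sessions, within 3% of the 1,054 stated. The stated figures give 6 × 1,824 / 1,054 ≈ 10.4. Ten is used below.

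**2. First few patients.** Assume that blocks of 2 and 4 are equally likely (the protocol does not say) and that the GP guesses the more probable arm.

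- Patient 1: 0.50.
- Patient 2: in a block of 2 the second card is fixed. In a block of 4, two of the three remaining cards are the other arm. So 0.5 × 1 + 0.5 × 2/3 = 0.833.
- Patient 3: if the first two cards match (probability 0.167), the block must be a 4 and the next card is certain. Otherwise it is even. So 0.167 × 1 + 0.833 × 0.5 = 0.583.
- Patient 4: after two matching cards it is again certain. After two different cards, the first block was a 2 with probability 0.5 / 0.833 = 0.6, which gives 0.6 × 0.833 + 0.4 × 1 = 0.90. So 0.167 × 1 + 0.833 × 0.90 = 0.917.

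**3. All ten patients, by exact enumeration.** Probability of a correct guess: 0.500, 0.833, 0.583, 0.917, 0.542, 0.875, 0.563, 0.896, 0.552, 0.885. The sum is 7.146, so the mean is **71%**.

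- With the probability of a block of 2 at 1/3 or 2/3, the mean is 71% or 72%.
- Allocations known with certainty: **about 10%** (range 7% to 12%).
- Allocations predictable with probability at least 0.8: 55%, or 41% if blocks of 2 have probability 1/3. This figure needs knowledge of the block sizes.
- The 71% does not need that knowledge. Simply guessing whichever arm is behind also gives 71% in simulation.

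**4. Alternatives**, simulated with the guess of the arm that is behind:

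| Scheme | Correct guesses |
|---|---|
| Blocks 2/4 within GP (as planned) | 71% |
| Blocks 4/6 within GP | 68% |
| Blocks 4/6/8 within GP | 66% |
| Blocks 6/8/10 within GP | 64% |
| Blocks 4/6/8 within practice, GP's own cards only (three GPs assumed) | about 56% |
| Same, RA who sees the whole sequence of about 30 | about 67% |
| Simple randomization | 50% |

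**5. Balance within a GP.** With Poisson recruitment of mean 10.1 per GP, the mean absolute difference between arms in simulation is about 0.6 participants for blocks 2/4 within GP and about 0.8 for blocks 4/6/8 within GP. For blocks 4/6/8 within practice it is about 1.8.

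**The case against.** The protocol has safeguards. The envelopes are opaque and numbered, two block sizes are mixed at random, GPs are told to judge suitability before opening, and each decline carries a reason. The RA has weighed and measured the patient beforehand, so declined patients are characterized. Nothing says that GPs are told the block sizes. To exploit the pattern, a GP would have to keep a running count over about six sessions and then act on it.

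Much of this stands, and it rules out three stronger readings that a reader might infer.

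- **That selection bias occurred.** The protocol gives no decline rate and no evidence that GPs acted on guesses. The discussion of fidelity checks reports GPs offering extra help to control participants, but that is an error of delivery after opening, not selection before it.
- **That the bias can be put in kg.** Suppose every GP holds back 20% to 50% of the less motivated half whenever the support arm is expected. The less motivated share in those consultations falls from 1/2 to 0.40/0.90 = 0.444 or 0.25/0.75 = 0.333, a shift of 0.056 or 0.167. Support is expected 71% of the time in one arm and 29% in the other, and the prognosis gap is assumed to be 1 to 2 kg. The bias is then 0.42 × 0.056 × 1 = 0.02 kg to 0.42 × 0.167 × 2 = 0.14 kg. If one GP in ten does this, it is a tenth of that. Each of these behavioural inputs is an assumption.
- **That a GP who declines a patient knows which card comes next.** The unopened card has not been seen. Patients also meet the RA before the consultation, so the next trial patient may already hold a different envelope.

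The safeguards still do not answer the point. The instruction on opening does not prevent inference from earlier cards. The planned comparison of people enrolled with people attending cannot show selection that differs between arms. The block sizes are also printed in an article that appeared in November 2013, about five months after recruitment began in June 2013 and inside the planned 46 weeks.

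**Conclusion.** The point holds as a weakness of the allocation scheme. The person best placed to predict the next allocation also has discretion over enrolment, and can be right about 71% of the time instead of 50%, with about 10% of allocations certain. These figures rest on about 10 participants per GP, and the 71% barely moves with the mix of block sizes. Selection by predicted arm is therefore possible, and adjustment for baseline weight would not correct it. Whether it happens, and by how much, cannot be learned from the protocol. The sample size calculation is not affected. The change is worth making for GPs still to start because it is cheap, and tabulating declines by arm would give direct evidence on whether selection took place.

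**What to change.** 1. **For GPs not yet started, drop blocks of 2** and use larger random blocks, for example 4, 6 and 8. Correct guesses fall from 71% to about 66%, a modest gain. The cost is a new list and new envelope sets, with slightly looser balance within a GP (about 0.8 instead of 0.6 participants). A GP term in the model can cover this, and the protocol already plans to explore GP effects.
2. **Do not tell GPs or RAs the new block sizes**, and do not publish them while recruitment runs.
3. **Write the envelope number on the withdrawal card for every declined patient.** After recruitment, the trial statistician tabulates declines, their reasons and the already measured weight and BMI by the arm in the returned envelope. If declining is unrelated to the arm, the returned envelopes should split about evenly. Include patients already seen where envelope numbers were kept. The cost is one extra entry per decline.

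Stratifying by practice is optional. It would cut the GP's correct guesses to about 56% (three GPs per practice assumed), but it gives up the stated aim of balancing consulting styles, and an RA who sees the whole sequence would still guess about 67% correctly. Having the GP mark suitability for every patient before opening would not help here, because the decision already comes before opening and the prediction rests on earlier cards.

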#### Unblinding

Due to the nature of this trial, it is necessary for the GPs and RAs to be aware of the patient’s treatment group allocation to ensure the correct intervention is provided. Thus, these personnel cannot be blinded to treatment. Patients and the members of the research team that will conduct follow-up assessments, however, will be blinded to treatment allocation.

As this is an open label trial the issue of unblinding the clinicians caring for the patient does not arise.

#### Withdrawal criteria

##### 

**Trial withdrawal** Participation in the trial is based upon patients consenting to take part. At the time of consent (see Recruitment of participants above) participants will be given a PIS to keep, which will provide details of what they should do if they no longer want to take part in the trial. The PIS will state that participants are free to withdraw from the trial at any point without it affecting their care and that they would not be contacted again by the research team. The PIS will include a telephone number for participants to contact the researchers for this or other reasons. Patients who have withdrawn will not be replaced but we will use their data up to the point that they withdrew unless they request that we do not do so. There are no withdrawal criteria other than patient or GPs request to withdraw.

##### 

**Treatment withdrawal** The main treatment is the offer of advice or support for weight loss from the GP. Participants cannot withdraw from receiving these interventions as they are a natural part of the consultation. Of course, it is possible that participants may choose not to return to the GP for further discussion of their weight. They may also choose not to attend a weight management intervention and, having initially attended, may choose not to complete a course of treatment. Such decisions will have no affect on the follow-up of participants in the trial.

### Definition of end of study

The end of study is the date of the last date of follow-up for the last patient. The appropriate standard operating procedure (SOP) (Primary Care Clinical Trials Unit [PC-CTU] SOP TM23), outlining the necessary procedures for trial closure, as written by the Clinical Trials & Research Governance Office, University of Oxford (CTRG), will be adhered to.

### Interventions

#### Intervention arms

After GPs have dealt with the patient’s original presenting complaint(s), they will briefly deliver one of two treatments, which the participant is randomly allocated to. The treatments include:

#### An ‘assistance-orientated’ treatment (intervention)

The GPs assistance-orientated treatment (that is, practical support) is aimed to last no more than a few seconds: “Did you know that the best way to lose weight is to go to Slimming World? I can refer you now for free on the NHS if you would like.” The choice of weight management service will mainly be determined by availability in the local area. In the Lighten Up trial, WW, RC, and SW each performed better than the control group [13].

If the person agrees to referral to the CWMS, the GP will ask the participant to make an appointment at reception to return in a month: “I know it can be difficult to lose weight, so I’d like you to return in a month to see how you’re getting on”. If the participant wants to try weight loss without assistance, the GP might say: “It’s fine for you to try to lose weight on your own but I know it’s hard. Would you make an appointment to return in a month to see how you are getting on?” This provides an opportunity to re-refer those who accepted referral but did not attend, refer those who tried to lose weight on their own but did not do well, prescribe orlistat to those who have followed the treatment program but not succeeded (in line with NICE guidance), and it lets the patient know their doctor is taking this seriously [30]. If the participant wants to discuss this with their GP, the GP will encourage the participant to make another appointment to do so (English GPs have 10 minutes per consultation).

Outside the context of the trial, we would envisage that the GP would make a referral to the weight management service in the same way s/he makes referrals to other services. We could envisage a system of direct booking, where the availability and days/times of local services are shown online on the GPs computer. However, because referral to weight management is uncommon, our GPs and patient representatives advised us it would be better to ask the research team to do this. We will aim for the RA in the practice to hold details of local groups that are available and make a booking immediately, to capitalize on the patient’s impulse to act. If this is not possible, we will arrange to telephone the participant at the earliest convenience with details of the options available.

The commercial weight management referral scheme typically consists of 12 vouchers enabling patients to attend classes for free (or use the online equivalent for anyone who does not want to or cannot attend groups). These services encourage weight loss via a healthy lifestyle such as increased physical activity, a reduced fat diet and offer group counseling for motivation and behavior change, with target setting for weight, activity, and energy intake. Intervention group participants will get 12 free sessions but are usually encouraged by the group leader to continue their involvement by paying, although in practice a minority do so. (We will obtain data on length of enrolment in the service from service providers and also from participants at follow-up.) Re-referral will be allowed within the rules operating in the PCT. Full details of the behavioral change techniques used by the three common services are available in the Lighten Up trial protocol [13].

#### An ‘advice-orientated’ treatment (control)

After considering the difficulties of a no-intervention control arm, we propose an advice-orientated treatment (that is, medical advice) such as: “It is important to lose weight because it would reduce your chances of getting heart problems, diabetes, and arthritis”*.* Other than no intervention, this appears to be the most common brief intervention offered currently and there is evidence that it is associated with attempts to lose weight. We believe it is polite and respectful and patients seem to find it helpful that their doctor passes on this kind of advice [25].

### Treatment providers

As noted above, the primary treatment (that is, delivery of either an assistance- or advice-oriented intervention) will be made by the participant’s GP. All GPs will receive trial specific training prior to commencing the study at their practice. We will train GPs using academic detailing methods, an established evidence-based technique for changing behavior [40]. The principal method of delivery will be via video-tutorials designed specifically for this trial, which will be available to GPs on a dedicated website before and during the trial. Each tutorial will be available to be viewed independently, rather than all having to be viewed at once, and also as downloadable audio files for alternative convenience. A similar approach has recently been established for smoking cessation (see http://www.NCSCT.co.uk/VBA); we intend to adopt a similar model.

The training video will consist of eight modules, lasting up to 2 hours in total: 1) the case for intervening in obesity; 2) the BWeL trial; 3) medical advice arm; 4) practical support arm part 1: the brief intervention; 5) practical support arm part 2: the review session at 1 month; 6) medical advice arm: the dedicated weight consultation; 7) practical support arm: the dedicated weight consultation; and 8) summary. The modules will be designed to address perceived barriers of the GPs to intervene in weight management. These barriers are that weight management is ineffective, which we will address by showing evidence that health risk is continuously associated with degree of overweight and that reduced weight reduces risk, even if the visible change is imperceptible. The barriers will also be addressed by evidence on the effectiveness of the commercial providers in the NHS referral schemes. We will also aim to address the lack of knowledge and hence confidence to intervene on weight management. This will be addressed firstly by reassuring GPs that we are not expecting them to undertake nutritional and physical activity assessments, and that the prime aim of the review session is reweighing, which is probably a key component of a weight loss intervention [30], and offer of referral/re-referral to the weight management services. Nevertheless, we recognize that patients might ask their GP for specific weight loss advice and our GP advisors were struggling to say more than “eat less, do more”*.* The modules will train GPs to deflect detailed questions about nutrition. We will provide GPs with a self-help guide published by the British Heart Foundation called ‘So You Want To Lose Weight…For Good’. We are not aiming to get GPs involved in behavioral change strategies or give particular or detailed advice, only allay concerns that might arise from offering patients a 10-minute review to discuss weight management. If there is any uncertainty about treatment delivery (for example, intervention content and methods of delivery) then GPs will be able to contact the research team for clarification.

To examine the fidelity of the interventions, we will seek the permission of both participants and GPs to audio-record the brief intervention component of a proportion of consultations (n = 5) by each GP. Most GPs will be familiar with recording their consultations as part of their training and most patients agree to this. To examine for evidence of consultation distortion, we will take the first 30 participants who have been recorded and compare the immediate post-consultation ratings of helpfulness and appropriateness to those not recorded. If evidence of distortion is found, we will not continue the recordings. Fidelity in the intervention group will be assessed by recording whether or not an offer of referral was made and whether or not there was supporting discussion (for example, encouragement to attend, advice on the superiority of the service over trying alone). Fidelity in the control group will be assessed on whether advice was given that linked weight loss to improved health and that no offer of referral to weight management was made.

Participants in the assistance-orientated intervention (that is, practical support) group will be offered referral to an evidence-based CWMS available in the NHS; for example, SW or RC. Immediately after the GP appointment, RAs at the GP practice will provide the intervention group participants with their weight management referral packs and assist booking the participant’s first appointment. Group leaders of these CWMS undertake rigorous weight management training through their organization and are expected to follow standard procedures.

